##### Study and concomitant medications

Important analysis criteria focus on compliance with the treatment protocol. In the inpatient setting, the study team will use the medical chart to keep a daily log of gabapentin and placebo dosing for each participant. Upon discharge, the participants, with weekly phone call assistance from the study team, will track study medications for the remainder of the study. The study team will document reasons for any deviations from the protocol-specified dosing plan. In addition, the study team will log all concomitant medications for the 6-month study period. In the inpatient setting this will be done by chart review and in the outpatient setting it will be collected during the weekly phone calls with participants. Information pertaining to the need for gabapentinoids use for pain management (if all other options fail) will be captured on the concomitant medication log and is critical for planning pain management in a future efficacy trial.

### Other considerations

As gabapentin is metabolized in the kidney, it is important to monitor renal function because some participants may have temporary renal impairment due to the initial injury that could require adjustment of gabapentin dose. All participants will undergo renal function testing as per clinical care. Testing typically occurs at the following minimum frequency while admitted to the different hospital settings: daily in the intensive care unit (ICU) acute care hospital and weekly in non-ICU acute care hospital. Testing during the inpatient rehabilitation and outpatient settings is at the discretion of the treating physician. Glomerular filtration rate (GFR) will be estimated using a dynamic formula since standard calculations are based on stable chronic disease (Physicians' Desk Reference). Study gabapentin will be renally dosed when needed (and documented). Control group medication will not be adjusted. A nephrologist will serve in an advisory role and provide input on participant safety issues.

Monitoring for other signs of poor gabapentin tolerance (such as confusion, sedation, edema, etc.) will occur at all study visits. Inpatient clinical teams will also be encouraged to report potential side effects. Gabapentin dose may be decreased by the unblinded investigators if needed.

Finally, this study using gabapentin falls under FDA Investigational New Drug (IND) exemption. Criteria for being exempt from filing an IND described under 21 CFR 312.2(b) *Exemptions* state that the clinical investigation of a drug that is lawfully marketed in the US is exempt if all the criteria in Table 4 apply.

**Table 4 T4:** CFR 312.2(b) IND exemptions.

**Criteria**	**Rationale**
The investigation is not intended to be reported to FDA as a well-controlled study in support of a new indication for use nor intended to be used to support any other significant change in the labeling for the drug.	We are not intending to report this data to the FDA to support a new indication or a change in labeling.
If the drug that is undergoing investigation is lawfully marketed as a prescription drug product, the investigation is not intended to support a significant change in the advertising for the product.	This study would not change any advertising.
The investigation does not involve a route of administration or dosage level or use in a patient population or other factor that significantly increases the risks (or decreases the acceptability of the risks) associated with the use of the drug product.	There is a long history of using gabapentin clinically in the broad SCI population via this route of administration and dosage level as well as up to 3,600mg daily.
The investigation is conducted in compliance with the requirements for institutional review set forth in part 56 and with the requirements for informed consent set forth in part 50.	This study will be conducted under the MHS IRB oversight.
The investigation is conducted in compliance with the requirements of § 312.7. (a) Promotion of an investigational new drug. A sponsor or investigator, or any person acting on behalf of a sponsor or investigator, shall not represent in a promotional context that an investigational new drug is safe or effective for the purposes for which it is under investigation or otherwise promote the drug. This provision is not intended to restrict the full exchange of scientific information concerning the drug, including dissemination of scientific findings in scientific or lay media. (b) Commercial distribution of an investigational new drug. A sponsor or investigator shall not commercially distribute or test market an investigational new drug. (c) Prolonging an investigation. A sponsor shall not unduly prolong an investigation after finding that the results of the investigation appear to establish sufficient data to support a marketing application.	This is not a new drug, we are not promoting any claims of safety or efficacy, we are not distributing anything commercially, and the data to be generated will not support a marketing application.

### Data analysis

#### Data security

Participants will be assigned a study code upon study entry. The linkage between the study code and participant identity will be stored in a secured REDCap database. Paper consent forms will be stored in a locked cabinet in a locked room with only study staff access. The study code will be used on all case report forms. Data will be evaluated for quality assurance in real time by the Principal Investigator. After which all data will be entered into a separate secured REDCap database for storage by the study coordinator. Quality assurance procedures will be repeated for all data entered into the database.

#### Primary data analysis

Primary data analysis will be conducted based on the benchmarks listed in Table 3. If all the quantitative benchmarks of success are met, it will be considered feasible to pursue an efficacy trial without significant protocol modification to determine the efficacy of early administration of gabapentin as an intervention for neurorecovery.

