#### Sample size

Studies analyzing feasibility are not intended to determine statistical significance, therefore traditional sample size calculations to power efficacy are inappropriate (21, 22). Rather, sample size should be large enough to yield useful data to answer the feasibility questions. There are several rules of thumb for determining a sample size for a feasibility study (typical range is 12–35 participants per arm; (23, 24). As described below, our most important neurologic outcome measure will be the ISNCSCI (all existing human data demonstrating effect of gabapentin on neurorecovery has been derived from the ISNCSCI). Differences in natural recovery due to injury severity could influence variability in ISNCSCI scores, with individuals that are AIS A or B being more similar than those that are AIS C or D (25). Therefore, we chose to stratify randomization into the 3 arms based on AIS grade (see Table 1). We will enroll 14 participants into each arm (with equal stratification of A–B and C–D in each arm). Therefore, our target sample size to complete the entire study will be 42.

**Table 1 T1:** Sample size and randomization cohorts.

**Arm**	**AIS A–B**	**AIS C–D**
Treatment 600 mg/day	7	7
Treatment 1,800 mg/day	7	7
Placebo	7	7

AIS, American spinal injury association impairment scale.

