#### Primary feasibility assessments

The primary endpoint of this trial is feasibility. Table 3 lists the measures and quantitative benchmarks of success for the following four feasibility questions:

Can the target population be recruited?Can the drug treatment protocol be delivered?Can the assessors remain blinded?Will participants complete the study?

**Table 3 T3:** Analytical questions, measures, and benchmarks of success.

**Question**	**Measure**	**Quantitative benchmark of success**
Can the target population be recruited?	Number screened/month; number enrolled/month; reasons for not enrolling	Screen an average of 4/month; Enroll an average of 1/month
Can the drug treatment protocol be delivered?	Proportion of enrolled who receive the full drug treatment protocol (placebo arm; two gabapentin dose arms); number of dosing deviations/arm; reasons for dosing deviations	70% enrolled in placebo arm receive full dosing protocol; 70% enrolled in each gabapentin arm receive full dosing protocol
Can the assessors remain blinded?	Number of occurrences of unblinding; reasons for unblinding	5% or fewer occurrences of unblinding
Will participants complete the study?	Retention rate; reasons for dropout; proportion of planned assessments completed	70% of participants stay enrolled until the end of the study and complete 3 of the 4 assessment visits

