### Limitations

We recognize that there are some limitations to this study protocol. One is that the placebo and gabapentin capsules are not identical. Participants could search online without the study team knowing and identify what treatment they are on based on the size, shape, color, and markings on capsules. By unblinding themselves this could create bias in the results. Also, the placebo and gabapentin capsules may taste different leading participants to identify which treatment they are on if they end up needing gabapentin for pain management after the 90-day treatment period. This could also create bias in the results.

The broad inclusion of all injury levels and severities and randomization scheme of grouping AIS A–B and AIS C–D is a limitation with regard to analyzing trends of neurologic recovery. As we are testing the feasibility of restricting/manipulating the use of gabapentin it is important that we understand the impact of that restriction for all injury levels and severities (e.g. ability to consent within the enrollment time window, potential swallowing difficulties) to be able to inform future trial enrollment criteria and randomization schema. Regarding the potential safety of gabapentin, it has been used broadly and at much higher clinical doses in all levels and severities of SCI so there is no strong rational to restrict inclusion based on injury level or severity. However, the heterogeneity of neurorecovery across injury levels and different AIS grades will have an impact on interpretability of efficacy results despite them intended to only be exploratory. A more appropriate randomization scheme for future trials may be to group AIS A by itself, AIS B–C together, and AIS D by itself.

Additionally, it is possible that even if all of the quantitative benchmarks of success are met regarding feasibility, protocol modification may be necessary to address heterogeneity of neurorecovery in a properly powered efficacy trial. We will have a strong understanding, however, of the ability to restrict the dosage of gabapentin and use a placebo for such a trial.

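### The feasibility rule promises an efficacy trial without significant protocol modification, which the Limitations say may not follow; its three-arm delivery test and undefined 5% unblinding limit also need clearer reporting

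*Protocol article*

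**What the plan says.** The protocol article, under Primary data analysis, rests the feasibility conclusion on the Table 3 benchmarks taken together: "If all the quantitative benchmarks of success are met, it will be considered feasible to pursue an efficacy trial without significant protocol modification". It states no consequence if a benchmark is missed.

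Table 3 (Primary feasibility assessments) sets the components. Delivery is judged arm by arm: "70% enrolled in placebo arm receive full dosing protocol; 70% enrolled in each gabapentin arm receive full dosing protocol". Retention is judged overall: "70% of participants stay enrolled until the end of the study and complete 3 of the 4 assessment visits". Blinding is given as "5% or fewer occurrences of unblinding", with no denominator. Recruitment is a monthly average of patients screened and enrolled.

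Under Sample size: "We will enroll 14 participants into each arm", and "our target sample size to complete the entire study will be 42".

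The Limitations section returns to the same condition and says that "even if all of the quantitative benchmarks of success are met regarding feasibility, protocol modification may be necessary", the reason being heterogeneity of neurorecovery. It adds that grouping AIS A alone, B with C, and D alone may be a more appropriate scheme for future trials than the A–B / C–D strata used here.

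**The concern.** The two sections draw different conclusions from the same event. A change of AIS stratification or eligibility is a protocol modification, and none of the four feasibility questions tests whether one is needed. A team that meets every benchmark and applies the rule as printed would report a conclusion that the article itself doubts.

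Two features of the rule also affect how its result should be read. First, it needs three separate arms of 14 to reach 70% on observed proportions, so chance alone can keep it from being met when delivery is modestly above target. Second, an unblinding percentage without a denominator can be computed in more than one reasonable way, and the ways can disagree on pass or fail.

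At stake is the message carried to the efficacy trial: what was shown to be feasible, for which arms, and with what uncertainty.

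**Working it through.** **The plan's own figure.** 3 arms × 2 AIS strata × 7 = 3 × 14 = 42, as stated. The article gives no error rates for the decision rule, so there are none to reproduce.

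**The two conclusions side by side.**
- Condition in both sections: all quantitative benchmarks met.
- Primary data analysis: an efficacy trial is feasible with no significant modification.
- Limitations: modification may still be necessary, with another AIS grouping named as possibly better.
- Scope of the benchmarks: recruitment, delivery, assessor blinding, retention. None measures heterogeneity of recovery or the adequacy of the strata.

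**Delivery threshold.** 0.70 × 14 = 9.8. Nine of 14 is 64.3% and fails; 10 of 14 is 71.4% and passes. Each arm therefore needs at least 10.

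**Chance that all three arms pass.** The true delivery rate p is not given. Assume the same p in each arm and independent arms. Let q = P(X ≥ 10) for X ~ Binomial(14, p); all three arms pass with probability q³.

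| True p | One arm, q | All three, q³ |
|---|---|---|
| 0.60 | 0.279 | 0.022 |
| 0.70 | 0.584 | 0.199 |
| 0.75 | 0.742 | 0.408 |
| 0.80 | 0.870 | 0.659 |
| 0.85 | 0.953 | 0.866 |
| 0.90 | 0.991 | 0.973 |

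q³ reaches 0.50 at p of about 0.769.

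**Adding retention.** 0.70 × 42 = 29.4, so at least 30 of 42 are needed. P(X ≥ 30) for Binomial(42, p) is 0.766 at p = 0.75 and 0.938 at p = 0.80. Multiplied by q³, this gives 0.408 × 0.766 = 0.31 and 0.659 × 0.938 = 0.62. The products treat retention and delivery as independent. The two are probably positively correlated, so the products are likely somewhat low.

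**Precision of a bare pass.** The exact (Clopper–Pearson) 95% interval for 10/14 is 0.419 to 0.916.

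**Unblinding denominator.** Table 2 plans four blinded ISNCSCI exams per participant: 42 × 4 = 168 exams.
- Per exam: 0.05 × 168 = 8.4, so at most 8 events.
- Per participant: 0.05 × 42 = 2.1, so at most 2 participants with any event.

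The true rate is not given. Assume a rate u per exam, independent across exams. The per-participant rate is then 1 − (1 − u)⁴.

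| u per exam | Per participant | P(≤ 8 of 168 exams) | P(≤ 2 of 42 participants) |
|---|---|---|---|
| 0.02 | 0.078 | 0.99 | 0.36 |
| 0.03 | 0.115 | 0.93 | 0.13 |
| 0.04 | 0.151 | 0.77 | 0.04 |

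The same conduct can pass on one reading and fail on the other.

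**The case against.** **The Limitations only qualify.** They say that modification may be necessary, for one disclosed reason; they do not take the conclusion back. That is fair, and a reader should not infer that the article withdraws its rule or has settled on a new stratification. The conflict of wording remains, because the rule is the text that will be applied.

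**The rule does not reject anything.** A reader might infer that the plan rejects a good protocol more often than not. The documents do not support that. Primary data analysis says only what follows when all benchmarks are met. If one dose arm misses, dropping or changing it would itself be a significant modification, so withholding the conclusion is consistent with the text. And failure of the delivery part is more likely than not only for a common true rate between 70% and about 77%.

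**False passes are rare.** A reader might take the single-arm pass probability of 0.28 at a true 60% as the rule's error rate. The rule needs all three arms, and that probability is 0.02.

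**The dose result will be visible.** Table 3 sets delivery benchmarks per arm, and Secondary data analysis reports by cohort. This stands. A rule needing only placebo and one dose is a design preference with a price: its pass probability, q(1 − (1 − q)²), is 0.69 against 0.41 at a true 75%, but 0.13 against 0.02 at a true 60%.

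**Intervals are often left to the analysis plan, and the trial is openly sized by rules of thumb.** Agreed. Their absence from a condensed article is not an error; showing them is advice on reporting.

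**The exam is the natural unit for unblinding.** The blinding questionnaire is completed after each exam and Table 3 counts occurrences. This stands, and it decides which denominator to adopt.

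**Conclusion.** The point holds in a limited form. The firm part needs no assumption: Primary data analysis and Limitations state different consequences of meeting all benchmarks, and four feasibility benchmarks cannot support a statement that the protocol needs no significant modification.

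The delivery part is a caution on interpretation. With 10 of 14 needed in each arm, the rule's delivery component is met about 41% of the time at a true 75%, 66% at 80% and 87% at 85%, assuming equal true rates and independent arms. A single-arm miss is therefore weak evidence of infeasibility when delivery is only modestly above target. This does not show that the 70% thresholds or the all-arms requirement are wrong.

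The missing denominator is a real ambiguity. At an assumed 3% unblinding per exam, independent across exams, the benchmark passes 93% of the time counted per exam and 13% counted per participant.

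**What to change.** 1. In Primary data analysis, limit the conclusion to what is tested. For example: *feasible as regards recruitment, drug delivery, blinding and retention; eligibility and AIS grouping to be reconsidered as noted in the Limitations.*
2. Report the delivery result for each arm with its exact confidence interval (for 10/14, 95% CI 42% to 92%). Leave the 70% thresholds unchanged.
3. In Table 3, state the 5% per blinded exam, which matches the questionnaire completed after each exam (at most 8 of 168 if all planned exams take place). Also report the number of participants with any unblinding.

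These are wording changes in Primary data analysis and Table 3. They need no new data, visits or participants. The downside is a slightly narrower stated conclusion.

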#### Secondary data analysis

Additionally, we will report the population demographics, adverse events, medications, outcome measures as well as pain characteristics and transitions. To do so we will calculate descriptive statistics for each outcome (e.g., frequency counts, percentages, means, medians, standard deviations, interquartile ranges, confidence intervals). We will report overall results within each cohort (placebo, 600, 1,800 mg gabapentin) as well as differences across cohorts. We will not test for statistical significance of efficacy because that is not the intent of this study.

In addition to using the descriptive statistics, we will perform a sensitivity analysis to inform a future efficacy trial. The literature suggests using the feasibility study's upper limit of the 80% confidence interval for the standard deviation when calculating the sample size needed for the future efficacy trial (52). We will analyze the blinded ISNCSCI total motor score results with confidence intervals at 75, 80, 85, 90, and 95% to get a preliminary, cautious view of efficacy/effect (22). This thorough sensitivity analysis will inform a sample size calculation for a future trial. Calculating the eligibility rate and the retention rate from this trial will also be helpful in estimating the duration of a future efficacy trial (22).

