### Randomization and intervention

#### Allocation and blinding

Participants will be randomized to 1 of 3 groups:

placebo,600 mg/day gabapentin, or1,800 mg/day gabapentin.

Group assignment will be stratified within each group based on AIS grade. A randomized stratified block design will be used with 3 blocks of size 7 within each cohort (AIS A–B and AIS C–D). A statistician will create a list under this design prior to enrollment of the first participant.

Blinded assessors will be designated for this study. The remainder of the study team will not be blinded to monitor all aspects of the trial. Blinding will be maintained by using the blinding plan described here to follow throughout the study.

The blinded assessors will be independent from the medical team and the research staff.Interactions between the blinded assessors and participants will be limited.Blinded assessments will be performed in a private room.The blinded assessors will be reminded prior to each assessment of the importance of blinding and to not engaging in extra “chit chat” with participants (and family/caregivers) or other study staff.Participants (and family/caregivers) will be informed of the importance of blinding overall at the beginning of the study and will be reminded prior to each blinded assessment to make sure he/she does not tell the blinded assessor(s) which group they are in.Blinded assessors will not review any previous blinded assessments.Blinded assessors will review the ‘Study Blinding Checklist' immediately before each blinded exam and will complete the ‘Blinding Verification Questionnaire' immediately after each blinded exam.If a participant becomes unblinded to his/her treatment group, every effort will be made to keep the blinded assessors blinded.If a participant develops neuropathic pain during the 90-day treatment window and the clinical team decides all other neuropathic pain treatments are ineffective, impractical, or contraindicated, study drug will be stopped and standard of care gabapentinoids may be used. The participant will not be withdrawn from the study, though, unless he/she desires to be withdrawn. Study drug will no longer be given, but any remain study visits will be completed. The blinded assessors will remain blinded of all knowledge that the study drug has been stopped.

Attempts will be made to blind participants, but as described below, the placebo and gabapentin capsules will not be identical.

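### The secondary analysis names only the treatment arm as its unit and does not carry the AIS stratification into the total motor score SD and confidence intervals

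*Protocol article*

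**What the plan says.** The Sample size section names the ISNCSCI as the most important neurologic outcome and gives this reason for stratifying: "Differences in natural recovery due to injury severity could influence variability in ISNCSCI scores, with individuals that are AIS A or B being more similar" (the comparison is with grades C and D). It continues: "Therefore, we chose to stratify randomization into the 3 arms based on AIS grade". Table 1 sets 7 participants per arm in each of AIS A–B and C–D, hence 14 per arm and 42 in all.

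Secondary data analysis lists descriptive statistics, including standard deviations and confidence intervals, and states the reporting unit: "We will report overall results within each cohort (placebo, 600, 1,800 mg gabapentin) as well as differences across cohorts". Here cohort means the treatment arm, whereas under Allocation and blinding it means the AIS stratum. The next paragraph builds on those descriptive statistics. It cites the literature for using the "upper limit of the 80% confidence interval for the standard deviation when calculating the sample size" of the later trial, and plans total motor score intervals at 75, 80, 85, 90 and 95%. It does not say whether that SD and those intervals are per arm or pooled over arms, adjusted for AIS or not, or on the score or its change.

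The Limitations section says that heterogeneity across AIS grades will affect how the exploratory efficacy results can be interpreted, and suggests grouping A, B–C and D in future trials. It does not connect this to the SD or the intervals.

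**The concern.** The design balances the arms on a factor chosen because it may drive the main neurologic outcome. The only analysis unit the article names leaves that factor out. Two things are at stake.

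First, this trial's own estimates. Stratified allocation removes the between-stratum component from the true variance of an arm difference. An interval built from an SD that still contains this component is too wide whenever the stratum means differ, whatever the next trial looks like.

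Second, the SD passed on. If the efficacy trial adjusts for AIS in its analysis, the matching input is the within-AIS residual SD. An SD that ignores AIS would make that trial larger than it needs to be, and the deliberate caution of the upper 80% limit would be multiplied on top.

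**Working it through.** **The plan's own figure.** 3 arms × 2 strata × 7 = 42, as stated. There is no power calculation to reproduce.

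**Inputs.** From the Sample size section: 7 + 7 per arm, three arms. Assumed, because the article gives neither an SD nor a stratum difference: a common within-stratum SD s, and a stratum mean difference of d × s with d from 0 to 2.

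**Variance when AIS is ignored.** For two equal strata the population variance is s²(1 + d²/4). For the sample variance of one arm of 14, the between-stratum sum of squares is 14 × d²s²/4 = 3.5d²s² on 13 degrees of freedom, so the expectation is s²(1 + 3.5d²/13). A simulation of 200,000 arms gave 1.065, 1.267 and 2.074 at d = 0.5, 1 and 2, in agreement. Sample size for a difference in means is proportional to the variance, so the same factor applies to it.

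| d (assumed) | 1 + d²/4 | 1 + 3.5d²/13 | SD ratio | Rise in future N |
|---|---|---|---|---|
| 0 | 1.00 | 1.00 | 1.00 | 0% |
| 0.5 | 1.06 | 1.07 | 1.03 | 6–7% |
| 1 | 1.25 | 1.27 | 1.13 | 25–27% |
| 1.5 | 1.56 | 1.61 | 1.27 | 56–61% |
| 2 | 2.00 | 2.08 | 1.44 | 100–108% |

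The SD ratio is the square root of the third column. Apart from a small change in the t quantile, it is also the ratio of unadjusted to AIS-adjusted interval width for an arm difference.

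**Upper 80% limit of the SD.** The factor is √(df/χ²), with χ² at its 10% point for a two-sided interval and its 20% point for a one-sided limit. The article does not say which is meant.

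| SD estimated from | df | Two-sided | One-sided |
|---|---|---|---|
| One arm-by-stratum cell of 7 | 6 | 1.650 | 1.398 |
| One arm, ignoring AIS | 14 − 1 = 13 | 1.359 | 1.227 |
| One AIS stratum, pooled over arms | 21 − 3 = 18 | 1.287 | 1.183 |
| All six cells, residual | 42 − 6 = 36 | 1.185 | 1.119 |
| Model with arm and AIS | 42 − 4 = 38 | 1.179 | 1.116 |
| Arm only, pooled over arms | 42 − 3 = 39 | 1.176 | 1.114 |

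Adding AIS to an arm-only model moves the two-sided factor only from 1.176 to 1.179. Estimating the SD in one arm instead of pooling over arms costs much more: against the six-cell residual, (1.359/1.185)² = 1.31 in sample size even at d = 0, or (1.227/1.119)² = 1.20 with a one-sided limit.

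**Illustration only.** Take a within-stratum SD of 15 (assumed), a difference of 6.3 points (the observational one-year figure in the Introduction), two-sided 5% and 80% power (assumed). Then n per arm = 2(1.960 + 0.842)² × 15²/6.3² = 89 with the within-AIS SD. Multiplied by the third column of the first table, this becomes 95, 113, 143 and 185 at d = 0.5, 1, 1.5 and 2.

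**The case against.** A reader might infer that the article plans the SD and the 75–95% intervals pooled over AIS. It does not say so. The sentence naming the arms closes a paragraph on descriptive reporting; the SD and interval sentences come next and fix no unit. Covariates are often left to an analysis plan, and this is a condensed article. This stands, and it limits the point to what the article does not carry through. It does not remove the point: the interval paragraph builds on the descriptive statistics, and the only unit offered is the arm.

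A reader might also infer that the next trial will be oversized. That depends on its analysis. Stratified randomisation alone does not shrink the SD in an unadjusted comparison; there, in the same case mix, the overall SD is correct. Nor would an A–B / C–D residual SD exactly match the A, B–C, D grouping suggested under Limitations. Both points stand.

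The stated rationale speaks of variability, which may mean unequal spread and not a shift in means. The calculation assumes a mean shift with equal spread. If spreads differ, a single residual SD is only an average, which is a reason to show the SD by stratum as well.

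Finally, the upper 80% limit is intended caution and no fault of the plan, the Limitations section already discloses AIS heterogeneity, and the SD can be recomputed from the same data later. These points lower the weight of the concern. The disclosure still does not say how the SD or the intervals should be computed.

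**Conclusion.** The point holds in a limited form. The article does not carry its own stratification factor into the total motor score SD and intervals. If the stratum means differ, unadjusted arm-difference intervals are wider than the design allows; this does not depend on the next trial. The effect on the next trial's size is conditional on an AIS-adjusted analysis there.

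The direction is secure given a difference in means. The size is not known: from no effect at d = 0 to roughly a doubling of the future sample size at d = 2, all under an assumed d and equal within-stratum spread. The consequence is confined to a secondary output and, if it occurs, errs towards a larger future trial. The Table 3 benchmarks, which decide feasibility, are unaffected.

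**What to change.** Add to Secondary data analysis that total motor score differences between arms and their 75–95% intervals come from a linear model with arm and AIS stratum (A–B, C–D) as randomised. State whether the outcome is the score or its change, and whether the 80% limit is one- or two-sided.

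For an AIS-adjusted efficacy trial, take the upper 80% limit of that model's residual SD, pooled over arms. Show the SD for A–B and for C–D as well, each pooled over arms (18 df) and not in cells of 7, where the limit is too loose to be useful. Report the overall unadjusted SD and intervals alongside, for use if the next trial is analysed without adjustment. Use one word for arm and another for AIS stratum.

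The cost is a sentence or two, one extra model and one degree of freedom for the stratum (39 to 38). No new data are needed.
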